#### Sample size and power calculation

The sample size for this study was based on estimating an effect on the primary outcome, the self-reported percentage of time spent on preventive tasks. Using a one-sided Pearson’s chi-squared test of proportions at alpha = 0.05, assuming 0.1 and 0.25 of the total percentage of working hours per week being assigned to prevention tasks in the control and in the treatment groups, respectively, 80 participants were needed in each group to achieve a statistical power of 0.8. Considering a loss to follow-up of 20%, this study would require a sample size of 200 individual participants, of which half in the control and half in the intervention condition. Taking into account that each peer group consists of approximately eight people, this corresponds to approximately 25 peer groups. This analysis was done using the procedure power in SAS, version 9.4, and in consultation with an experienced statistician.

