#### Effect evaluation

##### Outcome measures

The primary outcome is the execution of preventive tasks aimed at the prevention of work-related mental health problems. This will be assessed by means of the self-reported number of hours spent on each of these tasks, and the self-reported percentage of time spent on prevention, absence and reintegration guidance, and other tasks (e.g. teaching responsibilities). Moreover, OPs will be asked if they would like to spend more time on prevention (ranging from “no, less time” to “yes, considerably more time”). If they want to spend more time on prevention, they will be additionally asked on what specific tasks (e.g. open consultation hour, advising about occupational health policy). Furthermore, questions derived from an existing questionnaire of the Netherlands Society of Occupational Medicine will be used [18]. This questionnaire consists of various statements concerning preventive tasks, whereby OPs must indicate to what extent the statement applies to their situation (ranging from “this applies to a very small degree” to “this always applies” and to what extent they consider it important (ranging from “very unimportant” to “very important”. A selection of 20 statements (out of 58 in the total questionnaire) will be included in the questionnaire. Examples of these statements are: *“I regularly visit the workplace to monitor the interaction between work and health and to evaluate opportunities and risks.”* or *“I give my employers solicited and unsolicited advice about preventive tasks, to prevent and limit health threats”* [18].

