##### Data analysis

Data at baseline, 6 months (T1) and 12 months follow-up (T2) will be presented using descriptive statistics. To investigate the effectiveness of the intervention, differences between the intervention and control group in the outcomes at baseline, T1 and T2 will be analysed making use of longitudinal linear or logistic mixed models. If necessary, baseline differences between the intervention and control group will be adjusted for. Consistent with the design of the cluster-RCT and to avoid bias, analyses will be performed following the intention-to-treat principle. This means that all participants randomized will be kept in the groups they were randomized to, regardless of the intervention they received in practice [23]. For the analyses a two-tailed significance level of < 0.05 will be considered statistically significant. All statistical analyses will be performed with SPSS software, version 28.0.1.1.

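### The sample size treats mean shares of working time as event proportions in a chi-squared test, so 80 per group and power 0.8 do not describe the quantitative primary outcome

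*Protocol article*

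**What the plan says.** The section on sample size and power calculation in the protocol article names the sizing outcome as "the primary outcome, the self-reported percentage of time spent on preventive tasks". The method opens with "Using a one-sided" Pearson test, described as a "chi-squared test of proportions at alpha = 0.05", and the effect is given by "assuming 0.1 and 0.25 of the total percentage of working hours per week being assigned to prevention tasks" in the control and treatment groups. The result is that "80 participants were needed in each group to achieve a statistical power of 0.8". Allowing for 20% loss, this becomes 200 OPs in about 25 peer groups of about eight.

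The section on outcome measures has OPs report hours per preventive task and "the self-reported percentage of time spent on prevention, absence and reintegration guidance, and other tasks". It defines no threshold that would turn either measure into a yes/no result.

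The section on data analysis states that outcomes "will be analysed making use of longitudinal linear or logistic mixed models", with "a two-tailed significance level of < 0.05 will be considered statistically significant". It does not say which model goes with which outcome. No SD for the percentage of time appears anywhere in the article.

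**The concern.** A chi-squared test of proportions needs one yes/no result per OP, and 0.10 and 0.25 would then be the fractions of OPs with the event. Here they are average shares of working hours, where every OP contributes a value between 0% and 100%. The variance of such a variable depends on how much OPs differ from one another. It is not fixed by the mean, as p(1−p) is for binary data.

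What is at stake is how the result will be read. If the trial finds no difference, readers will turn to this paragraph to see which difference it could have detected. As written, the paragraph gives the power for a comparison that the trial will not make.

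**Working it through.** **Step 1. Reproduce the stated figure.** Inputs from the article: p₁ = 0.10, p₂ = 0.25, one-sided alpha 0.05, power 0.8. The mean proportion is 0.175.

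n = [1.645·√(2·0.175·0.825) + 0.842·√(0.10·0.90 + 0.25·0.75)]² / 0.15²

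= [1.645·0.537 + 0.842·0.527]² / 0.0225 = 78.3, so 79 per group.

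Power at 80 per group is 0.808. With 20% loss, 80/0.8 = 100 per group, or 200 in total, and 200/8 = 25 groups. The stated 80 is therefore a binary-outcome figure, not a loosely worded comparison of means.

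**Step 2. The SD that this formula imposes.** √[(0.10·0.90 + 0.25·0.75)/2] = √0.139 = 0.372, about 37 percentage points. By arm it is √0.09 = 30 points (control) and √0.1875 = 43 points (intervention). These are the largest SDs possible for a 0–100% variable with means of 10% and 25%. They are reached only if every OP spends either none or all of the time on prevention.

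**Step 3. The same difference as a comparison of means.** n per arm = 2·(1.960 + 0.842)²·SD²/15², two-sided 0.05, power 0.8, before clustering and loss. All SDs are assumptions.

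| SD (points) | n per arm |
|---|---|
| 10 | 7 |
| 15 | 16 |
| 20 | 28 |
| 25 | 44 |
| 30 | 63 |
| 35 | 86 |

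Eighty per arm matches this formula only at an SD of about 34 points (two-sided) or 38 points (one-sided).

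**Step 4. What the planned size could detect with clustering included.** Inputs: 80 analysed per arm; 25 groups, hence 160/25 = 6.4 analysed per group and 23 degrees of freedom; ICC 0.05 (assumed); a single time point without baseline adjustment.

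- Design effect = 1 + (6.4 − 1)·0.05 = 1.27
- Standard error = SD·√(2·1.27/80) = 0.178·SD
- Smallest detectable difference at 80% power = (2.069 + 0.858)·0.178·SD = 0.521·SD
- Power for 15 points from the noncentral t distribution with noncentrality 15/standard error

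| Assumed SD (points) | Detectable difference (points) | Power for 15 points |
|---|---|---|
| 10 | 5.2 | > 0.99 |
| 15 | 7.8 | > 0.99 |
| 20 | 10.4 | 0.98 |
| 25 | 13.0 | 0.90 |
| 30 (extreme) | 15.6 | 0.77 |
| 37 (all-or-nothing limit) | 19.4 | 0.58 |

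**The case against.** The strongest reply is that the error is conservative. Because the binary variance is the ceiling for these means, the method taken alone yields more OPs than a comparison of means would need. The low-power rows sit at or near an all-or-nothing split of working time. That is hard to reconcile with the article's own description of OPs, whose work is mostly absence and return-to-work guidance and who divide their time between several kinds of task. At SD 20 or less, power for 15 points is at least 0.98 with ICC 0.05, about 0.95 with ICC 0.10 and 0.88 with ICC 0.20. The planned analysis is also valid whatever formula was used for sizing. All of this stands. It rules out calling the stated size unrelated to the endpoint, and it rules out saying that nothing can be inferred about adequacy.

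A reader might go further and infer that the trial is underpowered. This error does not support that, because on its own it acts in the opposite direction. The absent clustering allowance and the one-sided sizing of a two-sided analysis do push towards too few OPs, but they are separate matters. They enter here only because a corrected calculation has to include them.

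A reader might also say that the article commits itself to a linear model for this outcome. It does not: it names linear or logistic models without assigning them. Linear is the natural reading for a percentage per OP. A logistic model would need a dichotomy that the article does not define.

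Finally, the comparison of means above is simpler than the planned longitudinal model. If baseline and follow-up values correlate and baseline is used, the detectable differences would be smaller than those shown.

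The mismatch itself survives: the stated power of 0.8 is not the power of the primary comparison.

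**Conclusion.** The point holds as an error of method and of a stated figure, not of arithmetic. Mean time shares were entered as event proportions, and the resulting 80 per group with power 0.8 does not describe a quantitative percentage of time per OP.

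The size of the discrepancy depends on an SD that the article does not give. For 15 points, two-sided and before clustering and loss, the need runs from 7 per arm at SD 10 to 63 at SD 30, against the stated 80. With an assumed ICC of 0.05 and SDs from 10 to 25 points, 80 analysed per arm could detect about 5 to 13 points, with power for 15 points of 0.90 or more. Power of 0.77 or lower appears at SD 30 and above, an extreme case. A larger ICC lowers these figures: at SD 25, power is 0.83 with ICC 0.10 and 0.71 with ICC 0.20. These values are conservative in that they take no gain from baseline or repeated measures.

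**What to change.** Replace the chi-squared calculation with one for a difference in mean percentage of time spent on prevention: two-sided alpha 0.05, a stated and justified SD, a stated ICC, 25 groups and 20% loss. For the planned 200 OPs, report both the power for a 15-point difference and the smallest detectable difference in percentage points, over a range of SD and ICC. State that the calculation uses a single time point, or include the assumed baseline correlation if it does not. Name the model intended for this outcome.

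The section on randomization has OPs complete the T0 questionnaire before groups are allocated. The SD and ICC can therefore be checked on pooled baseline data with no knowledge of arm.

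The alternative is to define a binary responder outcome, justify 0.10 and 0.25 as proportions of OPs, and analyse it as such. That would change the endpoint and is the larger step.

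The recommended change costs one recalculation and one rewritten paragraph. Enrolment, allocation and procedures stay as they are.

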### Step 5 – evaluation plan

#### Study design

To evaluate the implementation of the developed intervention, a two-armed cluster randomized controlled trial (RCT) will be conducted. The design of a cluster-RCT has been chosen, because the intervention will be delivered at a group level [16]. The OPs in the groups randomized to the intervention will participate in peer group supervision directed to implementation of preventive tasks targeting work-related mental health problems in their current practice. Groups of OPs randomized to the control condition will not get (initial) access to the intervention and materials. They will be put on a waiting list and participate in their peer group supervision as usual. The evaluation will consist of an effect evaluation and process evaluation. Each individual OP in both the intervention and control group will be asked to complete an online questionnaire at baseline (T0), after 6 months (T1) and after 12 months (T2). In addition, interviews will be held with a selection of participating OPs.

This study will be performed in accordance with the ethical guidelines and regulations laid down in the Declaration of Helsinki. Moreover, this study will be reported in adherence with the CONSORT Guidelines [17]. This study was approved by the Medical Ethics Review Committee of the Academic Medical Center Amsterdam, the Netherlands. The Medical Research Involving Human Subjects Act (WMO) does not apply to the above mentioned study. Written informed consent will be obtained via an online registration form from all participants prior to participating in this study.

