#### Randomization, treatment allocation and blinding

After each individual OP has given their written informed consent for participating in the evaluation and has filled in the baseline questionnaire (T0), randomization will take place at the level of the existing peer groups. Participating groups of OPs will be randomly assigned to (1) the peer group supervision plan directed to the implementation of preventive tasks targeting work-related mental health problems (intervention groups) or (2) the usual peer group supervision condition (control groups). The control groups will be put on a waiting list and receive the peer group supervision materials after the 12 months follow-up of this study. To avoid bias, the randomization process will be executed by two independent researchers. Researcher 1 will assign consecutive numbers to each participating peer group. A computer-generated randomization will then be performed by researcher 2, in order to assign each number to either the intervention or control group. This way, allocation to either one of the groups cannot be influenced. Because of the intervention, blinding for allocation on the level of the participant (OP) is not possible.

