### Methodological considerations

The chosen study design of a cluster randomized controlled trial is a suitable design since the intervention will be delivered at group level [16]. However, one limitation of this design is that participants within a cluster are more likely to resemble each other, and their results can therefore not be seen as independent [23]. In addition, cluster-RCTs have a higher risk of selection and dilution bias than individual RCTs [29]. These methodological limitations have been accounted for in this study by identifying the participants and obtaining their informed consent prior to cluster allocation [29]. This is possible, because existing peer support groups are recruited in this study. A limitation of the designed intervention is that it cannot tackle all identified barriers for the execution of preventive tasks. Some barriers are contextual factors, and related to the organization and financing of the occupational health care system in the Netherlands. These contextual barriers are not easy to solve within the current legislation and regulations. This study is thus conducted within the context of the current system.

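### The sample size makes no allowance for randomising peer groups, so the stated power of 0.8 is unsupported: within the plan's own calculation it fails once the intracluster correlation exceeds about 0.004

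*Protocol article*

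**What the plan says.** Under Study design, the Protocol article says that "a two-armed cluster randomized controlled trial (RCT) will be conducted". Under Randomization, treatment allocation and blinding, it says that "randomization will take place at the level of the existing peer groups".

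The section Sample size and power calculation uses a one-sided Pearson "chi-squared test of proportions at alpha = 0.05". Its inputs are shares of working time on prevention of 0.10 for control and 0.25 for intervention. It concludes that "80 participants were needed in each group to achieve a statistical power of 0.8". It allows for 20% loss, arrives at 200 OPs split equally, and then adds: "Taking into account that each peer group consists of approximately eight people, this corresponds to approximately 25 peer groups". It mentions no ICC, design effect or other allowance for clustering.

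Under Methodological considerations, the article accepts that "participants within a cluster are more likely to resemble each other, and their results can therefore not be seen as independent". The remedy it gives for the design's limitations is to identify and consent participants before groups are allocated. Under Data analysis, it plans longitudinal linear or logistic mixed models and states: "For the analyses a two-tailed significance level of < 0.05 will be considered statistically significant".

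**The concern.** The 80 per arm is a requirement for independent observations. Group size is used only at the end, to turn 200 people into 25 groups, and never to inflate the number of people. Consent before allocation guards against selective enrolment. It does nothing about correlation within groups or the information that this correlation removes.

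If OPs in the same group resemble each other, 80 analysed OPs carry the information of fewer than 80 independent ones. The article then offers readers a power figure whose derivation assumes what its own discussion denies. A null result could be read as coming from a trial with 80% power when the plan has not shown that it has it.

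**Working it through.** **Inputs from the article.** Proportions 0.10 and 0.25; one-sided alpha 0.05; 80 analysed per arm; 20% loss; about eight OPs per group; about 25 groups.

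**Assumed.** The ICC, which the article does not give. Analysed OPs per group: m = 8 × 0.8 = 6.4, which takes all eight members as enrolled and 20% as lost.

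**Step 1: reproduce the plan's figure.** For the Pearson test without continuity correction,

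power = Φ[(0.15·√n − z·A)/B]

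- Mean proportion: (0.10 + 0.25)/2 = 0.175
- A = √(2 × 0.175 × 0.825) = 0.537
- B = √(0.10 × 0.90 + 0.25 × 0.75) = 0.527
- One-sided z = 1.645

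Required n = [(1.645 × 0.537 + 0.842 × 0.527)/0.15]² ≈ 78.3, so 79 per arm, with power 0.803. At n = 80: (0.15 × 8.944 − 0.884)/0.527 = 0.869, so power is 0.808. Then 80/0.8 = 100 per arm, 200 in total, and 200/8 = 25 groups. The chain closes with a design effect of exactly 1, so no unreported inflation can be hidden in the 200.

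**Step 2: find the ICC at which 0.8 fails.** The slack is 80/78.3 = 1.022. Setting 1 + (6.4 − 1) × ICC = 1.022 gives ICC ≈ 0.022/5.4 ≈ 0.004. With m = 8 it is 0.022/7 ≈ 0.003.

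**Step 3: apply a range of ICCs.** Design effect = 1 + 5.4 × ICC; effective n = 80/design effect; the power formula is as in step 1. The two-tailed column uses z = 1.960.

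| ICC (assumed) | Design effect | Effective n per arm | Power, one-sided (plan's test) | Power, two-tailed |
|---|---|---|---|---|
| 0 | 1.00 | 80.0 | 0.81 | 0.71 |
| 0.01 | 1.05 | 75.9 | 0.79 | 0.68 |
| 0.02 | 1.11 | 72.2 | 0.77 | 0.66 |
| 0.05 | 1.27 | 63.0 | 0.72 | 0.60 |
| 0.10 | 1.54 | 51.9 | 0.65 | 0.52 |
| 0.20 | 2.08 | 38.5 | 0.54 | 0.41 |

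The value m = 6.4 is the milder choice. With m = 8, one-sided power is 0.70, 0.61 and 0.49 at ICC 0.05, 0.10 and 0.20.

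**The case against.** **The table may not describe the trial's actual power.** This is the strongest objection, and it stands. A reader might infer that the trial is clearly underpowered. The article does not support that. Its measure is a percentage of working time, and it plans mixed models. The plan's binary test implies a standard deviation (SD) of √(0.175 × 0.825) = 0.38, the largest that a variable between 0 and 1 with that mean can have. If 0.10 and 0.25 are mean shares of time, the SD could be much smaller.

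The article gives no SD. Taking SD 0.25 as an assumption, power = Φ[0.15/(SD × √(2 × design effect/80)) − z]. At ICC 0.20 the ratio is 0.15/(0.25 × √(2 × 2.08/80)) = 2.63, so one-sided power is Φ(2.63 − 1.645) = 0.84. At ICC 0.05, 0.10 and 0.20:

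| SD (assumed) | One-sided power |
|---|---|
| 0.20 | 0.995, 0.985, 0.95 |
| 0.25 | 0.96, 0.92, 0.84 |
| 0.30 | 0.88, 0.82, 0.71 |

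Two-tailed at SD 0.25, power is 0.92, 0.86 and 0.75. Whether power falls short therefore depends on an SD and an ICC that are both unstated.

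**The loss may be small.** At ICC 0.01 to 0.02 it is only 0.02 to 0.04. The article asserts resemblance within groups but does not size it. OPs may decline the evaluation, which would reduce the number analysed per group and so the design effect. Baseline and repeated measures could recover some power, although the sample size section takes no credit for them. Unequal group sizes and the small number of groups pull the other way.

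**A fuller plan may deal with clustering.** It may do so in the analysis model, but it cannot make this derivation right: the published figures follow completely from independence.

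**Conclusion.** The point holds as a fault in the planning calculation. The article derives power 0.8 for a cluster trial from a test for independent individuals, and its own discussion rejects that independence. Within that calculation the figure survives only to an ICC of about 0.004. Under assumed ICCs of 0.01 to 0.20 and 6.4 analysed OPs per group, it drops from 0.81 to between 0.79 and 0.54.

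What is shown is that the stated power is unsupported. It is not shown that the mixed-model analysis of a percentage outcome has less than 80% power. The one-sided planning test and the treatment of a mean percentage as a proportion of participants are separate matters. The first matters here only because a restated figure should match the two-tailed level of the analysis.

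**What to change.** In Sample size and power calculation, restate the power of the planned 200 OPs (about 25 groups):

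- Divide the 80 per arm by 1 + (m − 1) × ICC, with m the expected number of OPs analysed per group.
- State the assumed ICC and a range around it.
- Compute at the two-tailed 0.05 level given under Data analysis. On the existing binary calculation with m = 6.4, that is about 0.71 at ICC 0, 0.60 at 0.05 and 0.52 at 0.10. Label the figures as belonging to that calculation.

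The baseline questionnaire is completed before randomisation, so the ICC of the primary measure can be estimated from the pooled baseline data and reported with its interval as a check on the range. It should not become a single updated value. With 25 groups of eight and an ICC of 0.05, its standard error is about √[2 × 0.95² × 1.35²/(8 × 7 × 24)] ≈ 0.05. It also predates any correlation that the group sessions create.

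The cost is one rewritten paragraph and one calculation on baseline data. This correction requires no extra recruitment. The downside is a less favourable stated power.

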#### Study population and recruitment

The study population consists of OPs and will be recruited in two steps. First, we will recruit peer group supervision groups via the Netherlands Society of Occupational Medicine. Second, we will recruit individual OPs within each participating peer group and ask whether they want to participate in the evaluation. Thus, an individual OP can decide not to participate in the evaluation, but could still participate in the specific prevention-oriented peer group supervision meetings. OPs will be excluded from participating in this evaluation when: (1) They have an upcoming retirement or long-term leave (e.g. pregnancy leave) during the follow-up of this study (i.e. 12 months), or (2) They work fewer than 16 h per week as an OP. The latter requirement is to ensure OPs have enough time available to focus on their preventive tasks and change something in their working habits.

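### The sample size has no allowance for clustering although peer groups are randomised, so the stated power of 0.8 holds only if the intracluster correlation is essentially zero

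*Protocol article*

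**What the plan says.** The section Sample size and power calculation of the protocol article gives a complete chain:

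- Test: "Using a one-sided Pearson’s chi-squared test of proportions at alpha = 0.05".
- Rates: "assuming 0.1 and 0.25 of the total percentage of working hours per week being assigned to prevention tasks in the control and in the treatment" arms.
- Result: "80 participants were needed in each group to achieve a statistical power of 0.8".
- Attrition: "Considering a loss to follow-up of 20%, this study would require a sample size of 200 individual participants", split equally between the two arms.
- Conversion to groups: "Taking into account that each peer group consists of approximately eight people, this corresponds to approximately 25 peer groups".

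The section Randomization, treatment allocation and blinding makes the existing peer group the unit of allocation. Methodological considerations concedes that "one limitation of this design is that participants within a cluster are more likely to resemble each other" and draws the consequence that their results are not independent. It then says that the limitations of the cluster design were dealt with by identifying participants and taking consent before groups are allocated. Data analysis plans longitudinal linear or logistic mixed models at a two-tailed 0.05 level.

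**The concern.** A test of two independent proportions gives the right number only if every OP contributes independent information. Here whole groups are allocated and the intervention is delivered within them. Step 4 describes fixed groups, a trained chair, and advice from fellow OPs in setting goals. Some positive correlation within groups is therefore plausible, and the article says as much.

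The chain in the sample-size section closes at every step without a design effect, so no allowance is hidden in the rounding. The remedy offered under Methodological considerations, consent before allocation, protects against selection. It does nothing about the variance added by clustering.

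What is at stake is how the result is read. A null finding would be interpreted as coming from a trial with power 0.8, when that figure belongs to an individually randomised trial of the same size.

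**Working it through.** **Inputs from the article.** Rates p1 = 0.10 and p2 = 0.25, difference 0.15; one-sided alpha 0.05; power 0.8; 80 analysed per arm; 20% loss; about 8 OPs per group. **Not in the article:** any ICC. It is taken below as an assumption over a range.

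**1. Reproduce the plan's figures** (Pearson chi-squared test, normal approximation, pooled variance under the null, no continuity correction).

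- Mean rate 0.175. Null term: √(2 × 0.175 × 0.825) = 0.5374. Alternative term: √(0.10 × 0.90 + 0.25 × 0.75) = √0.2775 = 0.5268.
- n per arm = (1.645 × 0.5374 + 0.842 × 0.5268)² / 0.15² = 78.3, so 79 against the stated 80.
- Power at 80 per arm = Φ[(0.15 × √80 − 1.645 × 0.5374) / 0.5268] = Φ(0.869) = 0.808.
- Recruitment: 160 / (1 − 0.20) = 200. Groups: 200 / 8 = 25.

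The figures are correct for independent individuals. The design effect that 80 per arm can absorb is 80 / 78.3 = 1.022, which is almost nothing.

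**2. Add clustering.** Design effect DE = 1 + (m − 1) × ICC, and effective n per arm = 80 / DE. With 20% loss, m = 8 × 0.8 = 6.4 analysed per group.

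Example at ICC 0.05: DE = 1 + 5.4 × 0.05 = 1.27; effective n = 80 / 1.27 = 63.0; power = Φ[(0.15 × √63.0 − 1.645 × 0.5374) / 0.5268] = Φ(0.582) = 0.720.

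| Assumed ICC | DE (m = 6.4) | Effective n per arm | Power (m = 6.4) | Power (m = 8) |
|---|---|---|---|---|
| 0 | 1.000 | 80.0 | 0.808 | 0.808 |
| 0.01 | 1.054 | 75.9 | 0.789 | 0.784 |
| 0.02 | 1.108 | 72.2 | 0.771 | 0.760 |
| 0.05 | 1.270 | 63.0 | 0.720 | 0.696 |
| 0.10 | 1.540 | 51.9 | 0.646 | 0.609 |

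**3. Break-even ICC.** Power reaches 0.80 at DE = 1.022. That is ICC = 0.022 / 5.4 ≈ 0.004 with 6.4 per group, or 0.022 / 7 ≈ 0.003 with 8 per group.

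**4. The same inputs at the two-tailed level of the Data analysis section.** At ICC 0, power = Φ[(0.15 × √80 − 1.960 × 0.5374) / 0.5268] = Φ(0.548) = 0.708. This gap comes from the change of sidedness and not from clustering. It is shown because a restated figure should use the level at which the trial will be analysed.

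**The case against.** Four points can be made for the plan.

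- **The arithmetic is not wrong.** A reader might infer that 80 per arm fails to give power 0.8 on the plan's own inputs. The documents do not support that: those inputs give 0.808, and no ICC is stated from which a shortfall could be computed. The fault is an omitted allowance, and its size depends on an assumed ICC. At 0.01 the loss is small. This objection stands and limits the claim.
- **The figures are not the power of the planned analysis.** The outcome is each OP's share of working time, to be analysed by mixed models at a two-tailed level. For a share between 0 and 1 with a given mean, p(1 − p) is the largest possible variance, so the plan's inputs imply SDs of √0.09 = 0.30 and √0.1875 = 0.43. The true SD may be smaller. With 80 per arm, m = 6.4, a two-tailed 0.05 level and a common assumed SD, power is Φ[0.15 / (SD × √(2 × DE / 80)) − 1.96]. At SD 0.25 that is 0.92 for ICC 0.05 and 0.86 for ICC 0.10; at SD 0.35 it is 0.67 and 0.59. Baseline and repeated measurements may also recover some precision. A reader might infer that the trial is in fact below 80% power, but the article gives no SD or ICC that could settle this. The objection stands on that inference. It does not rescue the stated 0.8, which takes no credit for any of this.
- **Mixed models handle clustering.** A model that includes peer group gives honest standard errors. It does not restore the information lost, so this does not help the stated power.
- **Groups can be added.** Eight per group is full membership, while the section Study population and recruitment says "Thus, an individual OP can decide not to participate in the evaluation" and also excludes some members. About 25 groups is therefore an optimistic yield. A reader might infer a further loss of power, but the stated requirement is 200 OPs, the number of groups is only approximate, and no participation rate is given. This is a remark on feasibility and not part of the power claim.

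**Conclusion.** The point holds in this form: a cluster-randomised trial was sized as if the OPs were independent. The 80 per arm, 200 in total and about 25 groups are the figures for individual randomisation, with essentially no margin for clustering. On the plan's own one-sided comparison of 0.10 with 0.25, power is 0.81 only at ICC 0. It falls below 0.80 above an ICC of about 0.003 to 0.004, and ranges from 0.79 to 0.65 for ICCs of 0.01 to 0.10 with 6.4 analysed per group.

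This rests on the assumed ICC range, equal group sizes and the plan's binary variance held fixed. Given those, a positive ICC can only lower power. Because the article states the calculation in full, the omission is not a detail left to a longer document. The statement that the cluster limitations were accounted for is also wrong as regards non-independence, since the measure named addresses selection only.

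**What to change.** 1. In Sample size and power calculation, restate the power, or the smallest detectable difference, at the planned number of groups. Use a design effect of 1 + (m − 1) × ICC with m about 6.4 analysed per group, over a stated ICC range such as 0.01 to 0.10.
2. Put that restatement on the same footing as the Data analysis section: two-tailed 0.05, and the scale on which the primary outcome will be modelled, with the assumed SD stated if that scale is continuous.
3. In Methodological considerations, confine the accounted-for statement to selection, and say how non-independence enters the sample size and the analysis.
4. Optionally, note that eight per group is full membership and give the participation rate on which the number of groups rests.

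The cost is one rewritten paragraph and one corrected sentence. No extra enrolment is required. On the plan's present binary basis the stated power becomes less favourable. Holding 0.8 by design instead would be a separate decision: inflating the 80 per arm by the design effect and for 20% loss (2 × 80 × 1.27 / 0.8 = 254 OPs, about 32 full groups, at ICC 0.05) shows the scale.
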